### Materials

All outcome measures are completed at all three time points.

#### Primary outcomes

*Social anxiety*. The Social Anxiety Scale for Adolescents (SAS-A)^18^ will be used to assess social anxiety. The SAS-A contains 22 statements that are rated on a five-point Likert Scale (eg, I worry about what others say about me; I get nervous when I meet new people). A high score indicates high levels of social anxiety. The SAS-A contains three subscales, namely, fear of negative evaluation (FNE), social avoidance and distress in new situations (SAD-new) and social avoidance and distress in general (SAD-general). Cronbach’s alphas are satisfactory for the subscales, being α=0.91, 0.83 and 0.76, respectively.^18^ Further research also yielded satisfactory Cronbach’s alphas of *α*=0.89, 0.80 and 0.70 for FNE, SAD-new and SAD-general respectively.^19^

*Body esteem*. The subscale ‘appearance’ from the Body Esteem Scale For Adolescents and Adults (BESAA)^20^ is used to assess participant’s attitudes and feelings about their appearance. A higher score indicates more satisfaction with one’s appearance. This subscale consists of 10 statements, such as ‘I like how I look in photos’. The items are rated on a five-point Likert Scale ranging from ‘never’ to ‘always’. The subscale demonstrates excellent internal consistency in a sample of American girls (*α*=0.92) and boys (α=0.90)^21^ and in a sample of Dutch university students (α=0.90).^22^

#### Secondary outcomes

*Aspects of self-worth*. The Dutch version of the Self-Perception Profile for Adolescents,^23^ the Competentiebelevingsschaal voor Adolescenten (CBSA),^24^ will be used to assess different aspects of self-worth. The CBSA consists of eight specific domains and a global self-worth subscale. The specific domains are scholastic competence, social competence, athletic competence, physical appearance, job competence, romantic appeal, behavioural conduct and close friendship. The CBSA consists of 35 items, each consisting of two contrasting statements (eg, some teenagers are *not* happy with the way they look, BUT other teenagers *are* happy with the way they look). The adolescent is asked to pick the statement that is most representative of them and choose whether the statement is ‘sort of true for me’ or ‘really true for me’. All domains demonstrate good to excellent internal reliabilities, ranging from *α*=0.74 to *α*=0.93. The global self-worth subscale also demonstrates excellent reliability, with *α*=0.80–0.89.^23^

*Perceived stigmatisation*. The Perceived Stigmatisation Questionnaire (PSQ)^25^ will be used to measure stigmatisation behaviours commonly experienced by people with a visible difference. The PSQ is divided into three subscales, namely, absence of friendly behaviour, confused/staring behaviour and hostile behaviour. These subscales amount to a total of 21 items concerning stigmatising behaviours, such as ‘people avoid looking at me’ and ‘people call me names’. Participants are asked to rate how often they experience certain behaviour on a five-point Likert Scale. A high score reflects high perceived stigmatisation. The three subscales have been established,^26^ and the PSQ has adequate reliability in a sample of children and adolescents with a visible difference (α=0.81).^27^

*Health-related quality of life*. The EuroQol-5D-5L (EQ-5D-5L)^28^ is used to assess health-related quality of life. The scale has five dimensions, namely, mobility, self-care, usual activities, pain/discomfort and anxiety/depression. Each dimension can be assessed on five levels, which range from no problems to extreme problems. The EQ-5D-5L has good absolute and relative discriminatory power and good convergent validity.^29^

*Life engagement*. The Life Engagement Scale^30^ will be used to measure the extent that worries or feeling bad about the way you look stops you from engaging in life activities such as going to a social event or doing sports. The scale consists of ten questions on which the adolescent can rate how much their worries or feeling bad about the way they look stopped them from doing activities on a four-point scale. A high score indicates less life engagement. This instrument was purposively constructed for adolescents with a visible difference. The scale has good internal consistency, with *α*=0.93 for girls and *α*=0.96 for boys.^30^

*Appearance-related distress*. The Mirror, Mirror (Spiegeltje, Spiegeltje)^31^ Questionnaire will be used to assess appearance-related distress. This questionnaire consists of 58 statements about appearance (eg, my appearance makes me insecure), with a five-point Likert Scale ranging from ‘never’ to ‘always’. The questionnaire also contains a section with 38 body parts where adolescents have to indicate on a five-point Likert Scale how happy they are with said body part (eg, skin colour and the mouth). A high score indicates more dissatisfaction with appearance. As this questionnaire is new and unpublished, it has not been validated. We aim to validate this questionnaire using the data obtained in this study.

*Depressive symptoms*. The Child Depression Inventory-2 (CDI-2)^32^ will be used to assess depressive symptoms. The questionnaire consists of 28 items with three answer options (eg, I am sad sometimes, I am often sad and I am always sad). The scale consists of the subscales emotional problems, divided into negative mood/physical symptoms and negative self-esteem, and functional problems divided into ineffectiveness and interpersonal problems. A high score indicates more depressive symptoms. The questionnaire has demonstrated excellent internal reliability both for 13–16 year olds (*α*=0.89) and for 17–21 year olds (α=0.85).^32^ The scale has good test–retest reliability (r=0.60).^32^

### Recruitment

Participants are recruited through several channels. The first is through patient organisations. Patient organisations will be approached and asked if they are willing to advertise the Dutch YP Face IT Study on their website and in their newsletters. If an adolescent is willing to participate, he/she is encouraged to send an email to the research team, providing his/her contact details. The adolescent will then receive an information package containing a patient information letter, an informed consent form and a response card. The second channel is through our website (www.faceitvoorjongeren.nl). On our website, adolescents can read information about YP Face IT and contact the research team. If they do so, they will receive an information package. The third channel is through the Erasmus MC-Sophia Children’s Hospital. Subjects will be drawn from the department of child and adolescent psychiatry/psychology, the department of plastic and reconstructive surgery, the department of oral and maxillofacial surgery and special dental care and the department of dermatology. Subjects will be informed about the study by their treating doctor/clinician. It will be explicitly stated that participation is voluntary and that they can withdraw from the study at any time should they wish to do so. After informing the potential participant, they will receive an information package. If a potential participant does not have regular appointments at the Erasmus MC-Sophia Children’s Hospital, we will send an information package to their home address.

A response card will be included in the information package. On this response card, adolescents can indicate whether they give permission to be contacted by the research team. If the response card has not been returned within 2 weeks, the research team will contact the adolescent.

If participants are willing to participate, they are asked to fill in a consent form. For participants younger than 16 years, both parents are required to sign the informed consent form. After receiving the informed consent form, the researchers will include the participant in the trial and send out the first set of online questionnaires.

Participants will receive a gift card worth €10, after completing the entire study. If a participant decides to withdraw from the study prematurely, the adolescent will not receive a gift card.

### Study design

A flow chart of the RCT is depicted in figure 1. Prior to baseline, the inclusion and exclusion criteria as mentioned before (with the exception of appearance-related distress) are queried in a telephone call with the parent or adolescent. Appearance-related distress is measured based on the questionnaires completed at T1 (baseline). Adolescents will receive an email with a link to all questionnaires, with the exception of the CBSA. They will receive this questionnaire by post. This procedure is the same for T2 (13 weeks, direct follow-up) and T3 (25 weeks, 3-month follow-up).

**Figure 1 F1:**
[figure not shown]
Flow chart of the study design. CAU, care as usual; YP, Young People.

After completing the questionnaires, screening for appearance-related distress will take place by the research team. The scores on the SAS-A, BESAA and CDI-2 are considered. For the SAS-A and the BESAA, adolescents that score 0.5–2.0 SD above average will be included in the study. For the CDI-2, we will include adolescents scoring in the 70th–90th percentile, as the manual states that this corresponds to subclinical symptoms of depression.^32^ Adolescents that score within the defined range for one or more of the questionnaires will be randomised into the study. Adolescents that score below this range will be excluded from participation. Adolescents that score above this range will be contacted by the research team to assess whether there are clinical psychological symptoms. A phone call is made to both the adolescent and one of his/her parents. During this phone call, the Diagnostic and Statistical Manual of Mental Disorders (DSM) criteria for depressive disorder, social anxiety disorder or another suspected diagnosis will be asked. If suspicions of clinical psychological symptoms arise, the adolescents are referred to the appropriate psychological care. If no clinical symptoms are present, the adolescent is randomised into the study.

Adolescents with subclinical symptoms will be randomised to either CAU or YP Face IT. Adolescents in the CAU group will receive CAU and will complete T2 at 13 weeks and T2 at 25 weeks. The CAU group will have the opportunity to complete YP Face IT after their participation in the study. Adolescents in the YP Face IT group will receive CAU and YP Face IT and will complete questionnaires immediately after completing YP Face IT (T2; 13 weeks) and 3 months after completing YP Face IT (T3; 25 weeks).

### Randomisation and blinding

Participants will be randomised to either the CAU or the YP Face IT group in a 1:1 ratio. Randomisation will be stratified by age (12–13, 14–15 or 16–17 years old). Randomisation will be done using a list with a random sequence, generated using a computer programme. With the stratification, six different types of blocks can be formed. Each block will independently vary between four and eight randomisation pairs. The adolescents are informed of the group they are randomised to through email. The researcher analysing the data will be blind to the randomisation and will not be involved in monitoring the adolescents in the intervention. This researcher also supervises data collection by students, who are not blinded. The participants, the clinical psychologist and students monitoring the adolescents in the intervention will not be blind to the treatment conditions. When contacting the research team, the adolescents are explicitly instructed not to talk about the group they were allocated to.

If, through monitoring, the research team suspects that a participant experiences clinically significant symptoms, unblinding may take place. The participant will be excluded from the study and will be transferred to more appropriate care.

Participants that drop out after randomisation will be asked if they are willing to complete the questionnaires at T2 and T3. They are in no way obliged to do so.

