**Methods and analysis:**

Participants are adolescents aged 12–18 with a visible difference and experiencing appearance-related distress. In this two-armed randomised controlled trial, 224 adolescents will be randomised to care as usual or YP Face IT. Adolescents will complete questionnaires at baseline, at 13 weeks and at 25 weeks. Primary outcomes are differences in social anxiety and body esteem between YP Face IT and care as usual. Secondary outcomes are differences in aspects of self-worth, perceived stigmatisation, health-related quality of life, life engagement, appearance-related distress and depressive symptoms between the two groups.

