### Participants

This study will be conducted in a Dutch academic hospital. The target group for this study is Dutch adolescents aged 12–18 with a visible difference and experiencing appearance-related distress. Recruitment will take place throughout the Netherlands.

Adolescents will be eligible for participation if they are aged between 12 and 18, have a visible difference and access to a computer with internet and experience appearance-related distress. The appearance-related distress is operationalised as an elevated score on either social anxiety or depression or a lower score on body esteem, as assessed by self-reports.

Exclusion criteria are a mental disability, reading ability below 12 years of age, visual impairments preventing comprehension of the online intervention, a clinical diagnosis of depression, psychosis, body dysmorphic disorder or an eating disorder and insufficient proficiency of Dutch. Furthermore, adolescents who receive face-to-face care by a psychologist will be excluded from participation.

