### Sample size

For the sample size calculation, we applied a mixed-model Analysis of Variance (ANOVA) procedure, with a power of 0.80, a two-sided alpha of *α*=0.025 (Bonferroni corrected for two primary outcome measures), a correlation between the repeated measurements of *r*=0.70 and three repeated linearly decreasing measurements. Bessell and colleagues^17^ reported effect sizes of *d*=0.83 for appearance and *d*=0.80 for anxiety in a study on Face IT. However, as we are not certain that we will obtain such a large effect, we will consider a medium effect of *d*=0.50. To detect a medium effect, 56 participants are needed in both groups. As dropout is typically high in eHealth interventions,^33 34^ we anticipated a dropout of 50%. Therefore, 224 participants are needed in total.

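### Eligibility is stated as age 12–18 but the randomisation strata end at 17, so either the strata or the eligibility wording has to change

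*Protocol article*

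**What the plan says.** Three statements in the Protocol article give the age range:

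- Abstract, Methods and analysis: "Participants are adolescents aged 12–18 with a visible difference and experiencing appearance-related distress".
- Participants, target group: "The target group for this study is Dutch adolescents aged 12–18 with a visible difference and experiencing appearance-related distress".
- Participants, eligibility criterion: "Adolescents will be eligible for participation if they are aged between 12 and 18".

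Randomisation and blinding then defines the strata: "Randomisation will be stratified by age (12–13, 14–15 or 16–17 years old". It sets the allocation ("Participants will be randomised to either the CAU or the YP Face IT group in a 1:1 ratio") from a computer-generated list and adds: "With the stratification, six different types of blocks can be formed".

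Study design places the check of the entry criteria, other than distress, in a telephone call before baseline. Randomisation follows later, after the baseline questionnaires have been completed and scored and, for high scorers, after a further call.

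Statistical analysis describes two-level models whose fixed effects are group, time and their interaction. The age stratum is not among them.

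**The concern.** A stratified list works only if every eligible person belongs to exactly one list before the next allocation is seen. The article states both the eligible range and the complete set of strata, and the two end at different ages. If 18-year-olds may enter, staff have no written rule for which list to use. If they may not, the published criterion tells recruiting clinicians, patient organisations and readers something different from what the allocation procedure assumes.

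The missing reference date adds to this. Because age is checked before baseline and allocation comes later, a participant who is 17 at the telephone call can be 18 when randomised.

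At stake is a clear allocation procedure and a correctly described population. The trial's error rate and power do not depend on it.

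**Working it through.** **Step 1. What the strata notation means.** The bands must be in completed years: if 12–13 ended at the 13th birthday, everyone aged between 13 and 14 would fall between two bands. So 12–13 runs to the 14th birthday, 14–15 to the 16th, and 16–17 to the 18th.

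**Step 2. Each age against the strata.**

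- Ages 12 and 13: first stratum.
- Ages 14 and 15: second stratum.
- Ages 16 and 17: third stratum.
- Age 18: no stratum.

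Read in the same notation, 12–18 covers seven single-year ages, of which six have a stratum and one does not. Read as 12 to under 18, there are six ages and all are covered. The mismatch is therefore confined to age 18, and whether it falls on the strata or on the eligibility wording depends on an upper limit that the article does not define.

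**Step 3. How many participants.** The article gives no age distribution.

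- If the limit is the 18th birthday at randomisation: 0.
- If 18 is included and ages are assumed uniform: 224 × 1/7 = 32, or about 14%.
- If 18 is included and ages are not uniform: fewer or more than 32. An older sample would exceed it.

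**Step 4. Whether the sample size depends on this.** The inputs under Sample size are "with a power of 0.80, a two-sided alpha of" "0.025 (Bonferroni corrected for two primary outcome measures", a correlation of 0.70, three measurements on a linear course, and d = 0.50. Take group differences of 0, 0.25 and 0.50 SD at the three time points, compound symmetry, and a 2-df group-by-time F test:

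- Sum of squared deviations of the differences from their mean (0.25): 0.0625 + 0 + 0.0625 = 0.125.
- Noncentrality at n = 56 per group: (56/2) × 0.125 / (1 − 0.70) = 11.67, with 2 and 220 degrees of freedom.
- Power: 0.799 at 56 per group and 0.807 at 57.
- Dropout: 112 / (1 − 0.50) = 224.

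The plan's 56 per group and 224 in total are reproduced, 56 within rounding. Age and strata do not enter, so resolving the mismatch either way leaves these figures as they are.

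**Step 5. The block count.** Six equals three strata times two, for instance times two arms. The article does not define a block type, so the count can be neither confirmed nor refuted from the text.

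**The case against.** The strongest reply is that an upper limit of 18 often means up to the 18th birthday. The eligibility criterion's wording allows that, three even two-year bands fit it exactly, and nobody eligible would then lack a stratum. This is a fair reading, and it rules out saying flatly that eligible 18-year-olds cannot be randomised. It does not remove the inconsistency. The abstract and the target-group sentence give 12–18 in the same style as the strata, where the upper figure is included, and nothing states a cut-off at the 18th birthday. On this reading it is the eligibility wording that needs correcting.

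A reader might infer four stronger things, none of which the article supports:

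- **Allocation outside the list, with concealment broken.** Nothing says this would happen. Putting an 18-year-old on the existing 16–17 list would keep the computer-generated 1:1 sequence, and only the label would be inaccurate.
- **A wrong stratum variable in the analysis.** The models described have no stratum variable.
- **An error in the six block types.** The phrase is unexplained, which is not the same as wrong.
- **Thirty-two as a ceiling on those affected.** It follows only from an assumed uniform age distribution.

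It can also be said that covariates are commonly left to the analysis plan, which is not shown. That stands to this extent: the absent stratum term is a recommended improvement to the model as described, not a contradiction in the article.

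**Conclusion.** The article contradicts itself on the upper age limit, or at best leaves it ambiguous. With 18 included, the strata are incomplete; with 18 excluded, the eligibility statements are wrong. One of the two must change, and the documents do not show which.

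The reach is limited. It concerns 18-year-olds only, in a number that cannot be derived from the article, and there is no basis for claiming material bias in the treatment comparison. The conclusion rests on reading the strata in completed years, which their notation requires, and on the absence from the article of any placement rule or reference date for age. It is worth correcting because the remedy is cheap.

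**What to change.** 1. Reconcile the abstract, Participants, and Randomisation and blinding in one of two ways, according to what was intended: relabel the existing top list as 16–18, or restate eligibility as 12 to under 18 wherever the age range appears. Relabelling needs no regenerated list, which matters because Trial status says that the trial began in September 2019.
2. State that age, for the stratum and for the upper limit, is age at randomisation.
3. Add the age stratum as a fixed effect in the multilevel models, so that the analysis reflects the stratified randomisation. With three strata this costs two parameters per model. No gain in precision is claimed here, since the article gives no figure for how strongly age relates to the outcomes.
4. Add a sentence explaining what the six block types are.

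The cost is a few sentences of clarification, one list label if 18-year-olds are eligible, and one extra model term. No recalculation of the sample size is needed.

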7. Looking at your progress	Summary session, with summary of all previous sessions.	SIST/CBT	7
8. Booster quiz	Quiz with 16 questions on all taught techniques.	SIST/CBT	13

CBT, cognitive–behavioural therapy; SIST, social interaction skills training; YP, Young People.

YP Face IT is designed as a self-help intervention, without any active guidance by a psychologist. Adolescents work through the sessions on their own. Parents receive a short description of each session and will receive the reminders, but are not involved in the sessions themselves.

Monitoring will take place to assess whether adolescents complete the homework assignments and whether they are struggling in any way with the intervention or their mental health. Monitoring will be done by an experienced clinical psychologist and a master’s student. Should we find that adolescents experience severe psychological symptoms, they are referred to other care that may better suit their needs.

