#### Care as usual (CAU)

CAU will consist of regular medical care. The type of the care may differ depending on the condition (eg, skin care for eczema and orthodontics for cleft palate). Psychological care is not part of CAU. However, medical personnel will monitor the adolescents’ well-being as part of CAU. They may refer the adolescents to a psychologist in case of suspicions of psychological problems. Adolescents that receive psychological care during participation in the study will not be allowed further participation.

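### Two rules end study participation after randomisation for reasons close to the primary outcomes; as worded they stop T2 and T3 data collection and work against the intention-to-treat analysis

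*Protocol article*

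**What the plan says.** All references are to the protocol article.

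- *Participants* sets an eligibility criterion: "adolescents who receive face-to-face care by a psychologist will be excluded from participation".
- *Care as usual (CAU)* carries a similar criterion into follow-up: "Adolescents that receive psychological care during participation in the study will not be allowed further participation". The same section says that "medical personnel will monitor the adolescents’ well-being as part of CAU", and these personnel may refer to a psychologist. Both arms are exposed to this route, because *Study design* states: "Adolescents in the YP Face IT group will receive CAU and YP Face IT".
- *Randomisation and blinding* covers suspected clinically significant symptoms found through monitoring, with possible unblinding: "The participant will be excluded from the study and will be transferred to more appropriate care". No arm is named.
- *Intervention* describes what the team monitors: homework, and "whether they are struggling in any way with the intervention or their mental health". *Randomisation and blinding* adds that the clinical psychologist and "students monitoring the adolescents in the intervention will not be blind to the treatment conditions".
- The next paragraph of *Randomisation and blinding* makes a voluntary offer: "Participants that drop out after randomisation will be asked if they are willing to complete the questionnaires at T2 and T3".
- *Statistical analysis* specifies multilevel regression by intention to treat, with 3 months (T3) as the primary time point. The only adolescents it leaves out of the analyses are those never randomised.

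**The concern.** Needing psychological care and showing clinically significant symptoms are both signs of a poor course, close to social anxiety and body esteem. A rule that ends participation at that point turns a bad outcome into a missing outcome. The multilevel model keeps such an adolescent's T1 score and so corrects part of the loss, but T1 does not carry what happened afterwards.

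If the two arms removed such adolescents at the same rate, the losses would cancel in the comparison. They may not. Usual-care staff can pick up problems in both arms, but the only research-team monitoring of mental health that the article describes takes place within the intervention and is done by unblinded staff. That would remove more poorly faring adolescents from the YP Face IT arm and make it look slightly better at T3. The plan already expects 50% dropout, so it has reason not to give up retrievable outcomes by rule.

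**Working it through.** **Yardsticks from the plan.** The plan gives no figure on this point. *Sample size* gives d = 0.50, r = 0.70, two-sided alpha 0.025, 56 per group and 224 in total. These stand: a group-by-time interaction test with between-arm differences of 0, 0.25 and 0.50 and r = 0.70 has power 0.799 at 56 per group, and 112/0.5 = 224. The standard error of the T3−T1 contrast with 56 completers per arm is about √(2 × 2(1 − 0.70)/56) = √(2 × 0.6/56) = 0.15 SD.

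**Assumptions (not in the document).** The worst 5% or 10% are removed, that is 0.05 × 112 = 5.6 to 0.10 × 112 = 11.2, or 6 to 11 adolescents in one arm. Removal acts on interim status Z before T2; T1 is kept; T1, Z, T2 and T3 all correlate 0.70; there is no true effect; higher scores are worse.

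**Formula.** The model predicts a removed adolescent's T3 from T1 with slope r. What T1 misses is E[T3 − rT1 | Z] = (r − r²)Z = (0.70 − 0.49)Z = 0.21Z. If a fraction f of the worst q is removed without follow-up, and c is the cut-off with upper tail q, then E[Z | retained] = −f·φ(c)/(1 − fq). The shift in an arm's T3 mean is 0.21 times this.

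**One arm only (f = 1 in YP Face IT, 0 in controls).**
- q = 5%: 0.21 × 0.1031/0.95 = 0.023 SD.
- q = 10%: 0.21 × 0.1755/0.90 = 0.041 SD.

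Simulation with 1,000,000 per arm gives the same values, and 0.024 and 0.048 when the T1 slope is estimated from completers. Against the design effect these are 0.024/0.50 = 5% and 0.048/0.50 = 10%. Without the T1 correction the shifts would be 0.70 × 0.1031/0.95 = 0.08 and 0.70 × 0.1755/0.90 = 0.14 SD.

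**Other scenarios.** A positive sign favours YP Face IT; shifts are for q = 5% / 10%.

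| Scenario | Shift (SD) |
|---|---|
| Usual care detects 40% in both arms, team detects all in YP Face IT | 0.014 / 0.026 |
| Usual care detects 40% in both arms, team detects 50% | 0.007 / 0.012 |
| Equal detection in both arms | 0 |
| YP Face IT only, half of those removed complete T2 and T3 | 0.011 / 0.019 |
| YP Face IT only, 50% random dropout in both arms, no follow-up of those removed | 0.021 / 0.041 |
| The same, with those removed followed up at 50% like everyone else | about 0 |
| Controls only removed | −0.023 / −0.041 |

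First row at 5%: the control shift is 0.21 × 0.4 × 0.1031/(1 − 0.02) = 0.009, and 0.023 − 0.009 = 0.014.

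**Power.** The effect is minor. On a change-score approximation, 0.880 with 56 per arm falls to 0.861 with 10% extra loss in one arm.

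**The case against.** Much of the opposing case stands.

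- **Intention to treat.** A reader might infer that removed adolescents are dropped from the analysis and that the plan contradicts itself outright. The article does not support that. Its only stated exclusion from the analyses is of adolescents never randomised, and it nowhere says that collected data are discarded. What remains is avoidable missing data at T2 and T3.
- **Follow-up.** The offer of T2 and T3 questionnaires comes directly after the exclusion rule, is not limited to voluntary leavers and may be meant to cover removed adolescents. If so, most of the problem disappears. But both removal rules are worded more strongly than dropping out, and staff could reasonably stop sending questionnaires.
- **Arm difference.** A reader might also infer that the exclusion rule applies to the YP Face IT arm alone. The rule names no arm, and its provision for unblinding would be odd if it concerned only adolescents watched by staff who already know the allocation. Differential removal is a plausible inference from where team monitoring is described, not a stated fact.
- **Size.** The removal rates are assumed, and screening already refers suspected clinical cases before randomisation, so actual rates may be lower. Even the ceiling is about a third of a standard error (0.048/0.15).
- **Estimand.** It can be argued that stopping at psychological care is a legitimate choice of estimand. But the plan itself chose intention to treat, and continued follow-up serves that choice.

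**Conclusion.** The point holds in a limited form. Two stated rules end participation after randomisation for reasons close to the primary outcomes. Read as written, they forgo T2 and T3 data that the intention-to-treat analysis needs. These are instructions in the text, not details left to a fuller document.

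The expected bias is small and its sign uncertain: at most about 0.02–0.05 SD in favour of YP Face IT, 0 with equal detection, and reversed if controls are removed more often. The ceiling assumes that 5–10% are removed, that they are exactly the worst scorers, that all leave before T2 from one arm only, and that none is followed up. The documents do not support reading this as a threat to the trial's conclusions. It should be changed because the remedy is cheap and the direction of the error cannot be known in advance. Confidence is moderate, because the reach of the questionnaire offer and the arm difference both depend on how the text is read.

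**What to change.** In *Randomisation and blinding* and in *Care as usual (CAU)*, replace the end of study participation with wording such as: the study intervention is stopped where clinically needed, and the adolescent is referred as now, remains in the study and is offered the voluntary T2 and T3 questionnaires. Analyse all randomised adolescents as randomised. Record psychological care received, and report referrals, removals and such care by arm. If the existing offer to dropouts was always meant to include these adolescents, one sentence saying so settles the follow-up question.

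Cost: a wording change reported to the ethics committee as an amendment, and questionnaires for perhaps 22 adolescents (10% of 224 = 22.4, assumed). Clinical referral is unchanged. Giving the gift card for completing these questionnaires is optional and would cost about 22 × €10 = €220.

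Downsides: care after referral becomes part of the T3 comparison and could dilute or inflate the contrast, depending on which arm receives more of it. Reporting it by arm makes this visible but does not remove it. As recruitment has started, adolescents already removed can be approached only if their T2 or T3 is still due.
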